##### Blood Processing

Plasma samples will be collected using sodium citrate as an anticoagulant at a concentration of 3.2%. Plasma and serum aliquots will be obtained within 3 hours of sample collection by centrifugation at 3,000 g for 10 minutes and 2,000 g for 10 minutes, respectively, at 25°C, and then they will be stored at -80°C up to the time of use. For specialized coagulation tests, a 20-minute double centrifugation will be performed.

##### Blood Count Test

The CBC is a routine examination of venous blood collected in tubes with EDTA anticoagulant and performed in our laboratory by automatic DxH 800 analyzer provided by the Beckman Coulter company (Brea, California).

The tool provides fast, reliable, and high-quality results thanks to Automated Intelligent Morphology (AIM) and advanced algorithms, and it avoids cellular interference with Coulter’s principle impedance and multi-angle scatter laser.

It analyzes the number of red blood cells (erythrocytes or RBC), white blood cells (leukocytes or WBC), platelets (thrombocytes), hematocrit (HCT), and hemoglobin (Hb) levels of the leukocyte formula (percentage of different white blood cells: neutrophils, lymphocytes, monocytes, eosinophils, and basophils). It determines the physical characteristics of the red blood cells by means of the following indices: MCV (average corpuscular volume), MCH (average corpuscular hemoglobin content), MCHC (Medium Corpuscular Hemoglobin Concentration), RDW (red blood cell distribution amplitude), and MPV platelets (mean platelet volume).

##### Measurement of Coagulation Factors

All routine coagulation factors such as DD, Fibrinogen, ATIII, aPTT, PT, and specialist test of coagulation as PC, PS, FII, FVIII, vWF, and LA will be performed by ACL TOP 750 analyzer. This instrument is fully automated, fast and reliable, and able to detect all coagulation, chromogenic, and immunological reactions using a photo optical detection system by HemosIL commercial kits (Instrumentation Laboratory Co.). This guarantees maximum precision and accuracy of the results with the transmission of data to the laboratory computer system.

##### Measurement of Complement Components: C3, C4, C4a, C9

Serum concentrations of complement C3 and C4 components will be evaluated with Cobas 8000 fully automated platform by Roche Diagnostics. This instrument is based on an immunoturbidimetric principle. The reference ranges include 90–180 mg/dL and 10–40 mg/dL for human C3 and C4, respectively. The sensitivity of the test is 4 mg/dL for C3 and lower than 0.02 g/L for C4.

The fragment C4-a and component C9 were separately quantified by sandwich enzyme-linked immune-sorbent assay technology (ELISA) using two different kits purchased by Nordic BioSite AB.

###### Sample Preparation

The serum samples have to be left for 2 hours at room temperature or overnight at 4°C before centrifugation for 20 minutes at about 1000 g, and the supernatant is collected and the test must be performed either immediately or stored at -80°C until use.

###### Assay Procedure

Before running the test, the reagents will be prepared and the samples will be diluted as required in the kit. In detail, the test is performed on a 96-well plate, pre-coated with anti-C4a or anti-C9 antibodies. Standards and diluted samples are added to each well and incubated at 37°C for 90 minutes followed by three incubations at 37°C by suitable washes: the first with 100 µl of biotin conjugated anti-C4a or anti-C9 antibody for 60 minutes, the second with 100 µl of HRP-Streptavidin Conjugate (SABC) working solution for 30 minutes, and the third with 90 µl of substrate (TMB) in dark for 15–30 min to visualize HRP enzymatic reaction. TMB is catalyzed by HRP and produces a blue colored product that changes to yellow after adding 50 μL acidic stop solution. The plate is read at 450 nm in a microplate reader. The density of yellow is directly proportional to C4a or C9 concentration of sample. The reference ranges are: 1.563–100 ng/mL and 0.234–15 ng/mL for human C4-a and C9, respectively. This assay has high sensitivity (< 0.938ng/ml) and excellent specificity.

##### Measurement of sEPCR

Plasma levels of sEPCR will be performed by quantitative sandwich enzyme immunoassay (ELISA) Kit (Cusabio Biotech CO., LTD.). The detection range established by the manufacturer ranges from 7.8 ng/mL to 500 ng/mL. The dosage has a sensitivity lower than 1.95 ng/mL and high specificity.

##### Measurement of Angiopoietin-1, Angiopoietin-2, FIII/TF, TM, Tie-2, VEGF

Angiopoietin-1, Angiopoietin-2, TF, TM, Tie-2, and VEGF biomarkers will be performed by Magnetic Luminex Assay multiplex kits supplied by R&D Systems, Inc. (USA) (**Figure 2**).

**Figure 2 f2:**
[figure not shown]
Luminex Assay Principle. The sample is added to the mixture of colored beads coated with specific antibodies that bind the analyte of interest, the biotinylated detection antibodies in turn bind the analyte, and an analyte-antibody sandwich is formed. Streptoavidin conjugated with phycoerythrin (PE) binds biotinylated detection antibodies. The analysis of the beads is carried out either in a double laser flow with the Luminex 200 instrument or inside a magnet with the Luminex MAGPIX analyzer. The signal strength of phycoerythrin is directly proportional to the concentration of the specific analyte.

It is a premixed multi-analyte human kit, which can be used to evaluate up to 50 human biomarkers in a single supernatant, serum, plasma, and cell culture sample. The test is based on quantification immunoassay and the innovation of this test is represented by the use of magnetic microparticles. Determined antibodies for the analytes of interest are pre-coated to each specific region of the microparticle labeled with different fluorophores.

###### Sample Preparation

Fresh and previously frozen serum or plasma samples require centrifugation at 16000 g for 4 minutes immediately before use. Samples should be diluted correctly as required by the kit.

###### Procedure Assay

The diluted microparticle cocktail will be suspended by inversion or on a shaker, then 50 µl of microparticle cocktail, 50 µl standard, and 50 µl of samples will be added to each well of the microplate and incubated for 2 hours at room temperature on a horizontal orbital shaker for microplates (0.12 Orbit) set at 800 ± 50 rpm. Using a magnetic device, three washes with 100 µl of wash buffer will be performed to eliminate unbound substances, and 50 µl of the biotinylated antibody cocktail specific will be added to the analytes of interest to each well for 1 hour at room temperature on the shaker set at 800 ± 50 rpm. The washes will be repeated and 50 µl of the streptavidin-phycoerythrin conjugate will be added (Streptavidin-PE) to each well. Then it will be incubated for 30 minutes at room temperature on the shaker set at 800 ± 50 rpm. Final washes will be performed to remove unbound Streptavidin-PE. Finally, the microparticles will be resuspended in 100 µl of Wash Buffer for 2 minutes on the shaker set at 800 ± 50 rpm and within 90 minutes the plate will be read using a Luminex^®^ MAGPIX^®^ or Bio-Rad analyzer. A magnet in the analyzer captures and holds the superparamagnetic microparticles in a monolayer. Two spectrally distinct light emitting diodes (LEDs) illuminate the microparticles. One LED excites the dyes inside each microparticle to identify the region, and the second LED excites the PE to measure the amount of analyte bound to the microparticle. A sample from each well is imaged with a CCD camera with a set of filters to differentiate excitation levels. Analysis with the Luminex^®^ 100/200™, Luminex^®^ FLEXMAP 3D^®^, or Bio-Rad Bio-Plex uses one laser to excite the dyes inside each microparticle to identify the microparticle region and the second laser to excite the PE to measure the amount of analytes bound to the microparticle. All fluorescence emissions from each microparticle as it passes through the flow cell is then analyzed to differentiate emission levels using a Photomultiplier Tube (PMT) and an Avalanche Photodiode. The assay has a higher sensitivity than the traditional ELISA and requires a smaller sample volume, which is fast and efficient.

##### Measurement of APLs

###### Measurement of Anti-Cardilipin (aCL) and Anti-β2 Glycoprotein I (aβ2GPI)

The semi-quantitative detection of aCL and aβ2GPI of both IgG and IgM classes will be evaluated in serum by Kit BioPlex 2200 System Antiphospholipid Syndrome (APS) supplied by BIO-RAD Laboratories, Marnes-la-Coquette, France. The test is based on the multiplex flow immunoassay that uses microspheres coated with aCL and aβ2GPI antigens. It is a fully automated test.

*Procedure assay:* The test requires two incubations steps at 37°C into a unique reaction vessel, separated by washing: in the first step the dyed microspheres are added to the diluted sample, and in the second step the IgG and IgM antibodies conjugated to phycoerythrin (PE) and added in the reaction vessel. The microspheres mixture passes in laminar flow and is analyzed by the detector with two lasers.

Signals from a laser classify the microspheres, while those from another laser measure the fluorescence of the conjugate. The system software converts the conjugate signal into a fluorescence value (RFI). The values of specific antibodies are established by the manufacturer and expressed in GPL/MPL (aCL) and U/mL (anti-Beta2GPI). Samples with values of aCL or aβ2GPI (either IgG or IgM) inferior to 20 are evaluated as negative, values ≥ 20 to 40 weakly positive, values ≥ 40 to 80 average positive, and values ≥ 80 to 160 strongly positive. The sensitivity and the specificity of aCL and aβ2GPI (IgG) test is 67.5% and 100%, respectively. The sensitivity and the specificity of aCL and aβ2GPI (IgM) test is 25.8% and 98.7%, respectively.

###### Measurement of Anti-Prothrombin IgG/IgM and Anti-AnnexinV IgG/IgM

The quantitative measurements of IgG/IgM class autoantibodies against AnnexinV and Prothrombin in the serum will be determined by an indirect enzyme linked immune reaction (ELISA) kit supplied by DRG International, Inc., USA. The measurement range of this ELISA test was established by the manufacturer for Anti-AnnexinV and Anti-Prothrombin IgG/IgM ranges from 0 to 100 U/mL. The cut-off for Anti-AnnexinV and Anti-Prothrombin IgG/IgM is 8 U/mL and 10 U/mL, respectively.

Samples with values of Anti-AnnexinV IgG/IgM <5 U/mL are considered as negative, with values between 5 U/mL and 8 U/mL as borderline, with values ≥ 8 U/mL as positive. Samples with values of Anti-Prothrombin IgG/IgM <10 U/mL are considered as negative and with values ≥ 10 U/mL as positive. Limit of detection of Anti-AnnexinV and Anti-Prothrombin is of 1U/mL either IgG or IgM. The specificity of Anti-AnnexinV is 95.8% and 96.7% for IgG and IgM test, respectively. The specificity of Anti-Prothrombin is 98% and 99.3% for IgG and IgM test, respectively.

##### RNA Extraction and Hybridization on Agilent Microarray

Total RNA extraction from sera will be performed by a column-based method that includes small RNAs and minimizes the carry-over of enzyme inhibitors typically contained in biofluids (miRNEeasy serum/plasma kit, QIAGEN) (**Figure 3**).

**Figure 3 f3:**
[figure not shown]
Workflow of circulating miRNA profiling. For circulating miRNA profiling blood samples from patients will be processed. In particular, circulating RNA will be extracted from serum samples with a column-based extraction method. Total and small RNA quality will be assessed by Bioanalyzer. Then, total RNA will be labelled for the hybridization to Human miRNA Microarray Release 21 (Agilent) containing probes for 2549 human miRNAs. Microarray data will be subjected to bioinformatic analysis to identify a signature of miRNAs differentially expressed. Deregulated miRNAs pathway analysis and correlations analysis with clinical variables will be performed.

Total RNA will be labeled and hybridized to Human miRNA Microarray Release 21 (Agilent) containing probes for 2549 human microRNAs from the Sanger database. Each slide is an 8 x 15K format (~15,000 features printed in an 8-plex format, eight individual microarrays on a 1” x 3” glass slide) printed using Agilent’s 60-mer Inkjet Technology, which, unlike competitive platforms, synthesizes 40–60-mer oligonucleotide probes directly on the array, resulting in high-purity, high fidelity probes. This miRNA platform requires small input amounts of total RNA—in the 100 nanogram range—because it uses a high-yield labeling method and does not require size fractionation or amplification steps that may introduce undesired bias during miRNA profiling.

Scanning and image analysis will be performed using the Agilent DNA Microarray Scanner (P/N G2565BA) equipped with extended dynamic range (XDR) software according to the Agilent miRNA Microarray System with miRNA Complete Labeling and Hyb Kit Protocol manual. Feature Extraction Software (Version 10.5) will be used for data extraction from raw microarray image files using the miRNA_105_Dec08 FE protocol. microRNA Microarray data will be subjected to stringent quality controls and then analyzed by the Bioinformatic Unit.

##### Real Time Polymerase Chain Reaction

We enable automated purification of DNA and RNA (Qiasymphony–Qiagen) from a broad range of sample types, amplifying the DNA sequences and then analyzing the products. For overcoming the challenges of limited samples and a costly analysis we will choose, when possible, Multiplex PCR that enables the amplification of more than one target in a single reaction using different reporters with distinct fluorescent spectra (Seegene Korea). Multiplex qPCR requires the use of probe-based assays, in which each probe is labeled with a unique fluorescent dye, resulting in different observed colors for each assay. The signal from each dye is used to quantitate the amount of each target separately in the same tube or well. The availability to multiplex therefore allows the measurement of the expression levels of several targets or genes of interest quickly. In particular, we will analyze the following markers by qPCR: Epstein Barr virus, human herpesvirus 6, Torque teno virus, varicella zoster virus, poliovirus, Picornaviridae family including rhinovirus and enterovirus, coronavirus, adenovirus, influenza virus, and respiratory syncytial virus, Chlamydia pneumoniae, Staphylococcus aureus, and enterotoxin A.

#### MRI Procedures

All RRMS patients will undergo the 3.0-T MRI within two weeks of enrollment. We will use DSC perfusion technique acquired during the first pass of gadolinium to estimate perfusion features inside the damaged tissue of relapsing and remitting MS patients.

DSC MR images will be acquired on the axial plane during the first pass of a standard-dose bolus (0.1 mmol/kg) of gadopentetate dimeglumine (Magnevist; Berlex Laboratories, Wayne, NJ, USA) with a gradient-echo T2-weighted echo-planar imaging sequence. A contrast will be injected at a rate of 3,5 mL/sec, followed by a 20-mL bolus of saline also at a rate of 3,5 mL/sec. A total of 60 images will be acquired at 1-sec intervals, with the injection occurring at the fifth image, for a total acquisition time of 2 min 16 s. The imaging parameters will be as follows: TR/TE = 2140/30 ms, flip angle = 30°, slice thickness = 4 mm, FOV = 280 mm, matrix = 128x128.

The following hemodynamic parameters will be obtained from the concentration–time curves: the relative CBV (rCBV, i.e., the fraction of the tissue volume occupied by blood), the relative CBF (rCBF, i.e., the volume of blood in a given amount of tissue per unit of time), and MTT (the average time it takes for the contrast agent to travel through the tissue vasculature, for the ideal case of an instantaneous bolus injection) by using NordicIce software package.

Thus, we will use the leakage correction function provided by NordicIce software to minimize this effect both on Gadolinium and on non-Gadolinium enhancing lesions, in which a subtle leakage of contrast agent cannot be excluded.

Finally, rCBF, rCBV, and MTT values will be extracted from different sites of the brain damaged by MS (hyperintense T2-w lesions, Gadolinium enhancing T1-w lesions, periventricular and frontal NAWM, thalamus, and putamen nuclei and head of the caudate bilaterally). To exclude interobserver and to minimize intra-observer variability, each data set will be reviewed by two expert radiologists at the same time (**Figure 4**).

**Figure 4 f4:**
[figure not shown]
DSC perfusion maps and their overlap with structural masks in an MS patient. **(A)**. AIF curve created by using global, automatic, and outside-artery technique **(B)**. Leakage map, obtained through the leakage correction function, to minimize leakage effect both on Gadolinium and no Gadolinium enhancing lesions **(C)**. a. CBV map; b. CBF map; c. MTT map. **(D)**. a. NAWM (red), obtained by subtracting from white matter (WM binary) masks the different types of lesions, linearly registered to CBV map; b. thalamus (yellow), caudate (green), putamen (light blue), globus pallidus (blue), obtained by using FIRST software, linearly registered to CBV map. AIF, arterial input function; CBV, cerebral blood volume; CBF, cerebral blood flow; MTT, mean transit time; NAWM, normal appearing white matter.

### Data Analysis

#### Sample Size Calculation

Overall 90 subjects (30 for each group) will be enrolled to compare the level of complement C4a (55). By using the ANOVA test, this sample size will allow detection of effect size values [delta=(miA–miB)/sigma] equal to at least 0.71, with a statistical power of 80%, to a level of significance of 5%.

#### Statistical Methods

Descriptive statistics will be used to summarize pertinent study information. Correlations between quantitative variables will be assessed with the Pearson r correlation. The associations will be analyzed by the Fisher exact test or Chi Square test for trends. Comparisons between disease subgroups and control group will be carried out for different variables, using either Student’s *t-*test or analysis of variance (ANOVA). If the ANOVA shows a statistical difference between subgroups, a post-hoc analysis with Bonferroni correction for multiple comparisons will be performed. For non-normally distributed data, non-parametric (Mann Whitney-U or Kruskal-Wallis-H) tests will be used. The level of significance is set at p ≤ 0.05 (SPSS version 20.0, SPSS Inc., Chicago, Illinois, USA).

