## Abstract

**Introduction:**

Multiple sclerosis (MS) is a demyelinating disease of the central nervous system with an underlying immune-mediated and inflammatory pathogenesis. Innate immunity, in addition to the adaptive immune system, plays a relevant role in MS pathogenesis. It represents the immediate non-specific defense against infections through the intrinsic effector mechanism “immunothrombosis” linking inflammation and coagulation. Moreover, decreased cerebral blood volume (CBV), cerebral blood flow (CBF), and prolonged mean transit time (MTT) have been widely demonstrated by MRI in MS patients. We hypothesized that coagulation/complement and platelet activation during MS relapse, likely during viral infections, could be related to CBF decrease. Our specific aims are to evaluate whether there are differences in serum/plasma levels of coagulation/complement factors between relapsing-remitting (RR) MS patients (RRMS) in relapse and those in remission and healthy controls as well as to assess whether brain hemodynamic changes detected by MRI occur in relapse compared with remission. This will allow us to correlate coagulation status with perfusion and demographic/clinical features in MS patients.

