**Additional secondary outcomes:**

To assess relative CBF, CBV, and MTT by DSC 3.0-T MRI in relapsing MS patients compared to remitting MS patients.To evaluate number and volume of enhancing lesions in relapsing MS patients compared to remitting MS patients.To evaluate the relationships between laboratory data, demographic/clinical (age, gender, disability and disease duration) features, and MRI perfusion findings in the patients’ groups.

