### Selection of Subjects

Subjects of both genders will be recruited in two centers: the Multiple Sclerosis Center of the Sapienza University of Rome and the Multiple Sclerosis Center of the IRCCS Regina Elena National Cancer Institute. The planned recruitment period will be of three years.

Prior to enrollment, all participants will be screened to check their inclusion and exclusion criteria.

Patient inclusion criteria will be:

Patients diagnosed with relapsing-remitting MS (93)Patients untreated or treated with only immunomodulatory therapy18–60 years old

Patient exclusion criteria will be:

pregnancyco-existing neoplastic, hematologic, thyroid, metabolic, thrombotic, or autoimmune diseasesdrug or alcohol addictedtherapy with immunosuppressive drugs, steroids, or any medication interfering with coagulation

We will evaluate 3 groups of subjects: 30 RRMS patients in relapse (Group I); 30 RRMS patients in remission, i.e., without relapse in the previous 2 months (Group II), and 30 sex- and age-matched healthy controls (Group III).

A relapse or exacerbation or “attack” was defined by the multiple sclerosis guidelines as a manifestation of new or worsened neurological symptoms lasting for more than 24 hours (94). Symptoms should be supported by subjective description and by objective clinical assessment with no other explanation for them. The relapse is separated from the previous “attack” by at least 30 days and usually persists for days or weeks, then slowly improves over weeks or a few months ending with partial or complete recovery, i.e., remission. MRI showed the new and/or active lesions in the majority of patients, and steroid therapy often accelerates the recovery of symptoms.

Relapse needs to be distinguished from a pseudo-exacerbation, which is defined as a temporary worsening of pre-existing symptoms without new MS-related neuroinflammation, thus an MRI does not detect active or new lesions (95). The causes of pseudo-relapses could be different and include infections with or without fever, increased body temperature due to over-exercising, sauna, hot shower/bath or weather, dehydration, hormonal changes during menstruation or severe psychological stress, surgery, trauma, medications, alcohol overuse, and several medical conditions as thyroid or other metabolic disorders. Pseudo-relapses usually last less than 24 hours and resolve after removing their triggering causes with no need for steroid therapy.

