On the other hand, healthy people, potentially research subjects, will have only blood sample collection for the pre-specified laboratory assessment; they will not undergo Gd-enhanced MRIs since it represents, in any case, a reasonable low risk related to the use of contrast. Patients will be seen and assessed for physical disabilities using the Expanded Disability Status Scale (EDSS) (97) and Multiple Sclerosis Functional Composite (MSFC) (98).

Each subject included in the study will remain anonymous for privacy reasons and identified by a progressive numeric code (ID number) (associated with their own name, surname, and date of birth in a separate database) so that all serum/plasma samples and MRI data will be treated and processed blindly. An ad-hoc secure database has been established to collect standardized data from different centers, data storage, and sensitive data protection.

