## Conclusion

In this study, it will be important to identify the exact links between activation of coagulation/complement system and brain hemodynamic changes with cerebral hypoperfusion.

We hypothesized that cerebral hypoperfusion in all forms of MS could be the result of the blood flow deceleration mostly in the venous vessel bed during brain inflammatory-thrombotic processes in the course of relapses. Systemic immune activation during the infections influences innate brain immunity and, consequently, adaptive immune response (79, 80). When recurrent and chronic infections, which manifest systemically with immunothrombosis (13), directly or indirectly involve the CNS, it could lead to acute and chronic neuroinflammation. Constant crosstalks between immune cells and coagulation are seminal for an effective immune response (12). While many efforts have been carried out to better define the function of innate immune cells in order to modulate their potential pathogenetic role in MS with specific therapeutic action (5, 6), the coagulant component of innate immunity, which is well studied in animals, has not been sufficiently evaluated in humans. Our working hypothesis is that relapsing patients could have a pro-coagulant condition that may be correlated with blood flow deceleration and the presence of serological indicators of ongoing infection. Whether or not we found correlations between laboratory and MRI parameters, we may see the difference between the relapsing and the remitting MS patient groups. One could argue that peripheral laboratory parameters measured in this study may not fully reflect nor be specific for pathophysiological events occurring in the CNS. However, we hypothesize and believe that events at the CNS level, particularly in MS, could partially represent or be a result of systemic diseases such as infections.

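### The coagulation–perfusion correlation is fixed as plain Pearson r with no handling of relapse status; if relapse and remission patients are pooled, it cannot separate a link from two group shifts

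*Protocol article*

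**What the plan says.** All references are to the protocol article.

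- **Method.** Statistical Methods names one correlation method: "Correlations between quantitative variables will be assessed with the Pearson r correlation". It mentions no group term, stratification or partial correlation.
- **Fallback.** The same section adds: "For non-normally distributed data, non-parametric (Mann Whitney-U or Kruskal-Wallis-H) tests will be used". Both named tests compare groups; neither is a correlation.
- **Aim.** The last of the additional secondary outcomes is "To evaluate the relationships between laboratory data, demographic/clinical (age, gender, disability and disease duration) features, and MRI perfusion findings". The sentence closes with "features, and MRI perfusion findings in the patients’ groups". The Abstract puts the aim this way: "This will allow us to correlate coagulation status with perfusion and demographic/clinical features in MS patients".
- **Who has data.** Selection of Subjects plans "30 RRMS patients in relapse (Group I); 30 RRMS patients in remission". Of the healthy controls it says "they will not undergo Gd-enhanced MRIs". The correlation can therefore use at most 60 people, half of them in relapse.
- **Hypothesis.** The Conclusion expects that "relapsing patients could have a pro-coagulant condition that may be correlated with blood flow deceleration".

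**The concern.** The study expects relapse to raise coagulation activity and to slow flow. If both happen, relapse patients sit at one end of both scales and remission patients at the other. A single Pearson r across the 60 then picks up the distance between the two clusters, even if a patient's coagulation level says nothing about perfusion within either cluster. A significant r could not be told apart from the plain fact that both quantities change in relapse.

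The Discussion part of the Abstract rests the value of the work on a link between coagulation or complement activation and hypoperfusion, so the reading of this r matters even though it is listed low among the outcomes.

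There is a second, separate gap. The plan allows for non-normal data when it compares groups but names no counterpart for correlations. If a marker is strongly skewed, Pearson r can miss a real monotone relationship.

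**Working it through.** **The plan's own figure.** The only stated design figure is the detectable difference of 0.71 SD in C4a (Sample Size Calculation: 30 per group, three groups, ANOVA, 80% power, 5% level). Take one group differing by d from two equal groups. The noncentrality is 30 × (2/3) × d² = 20 × 0.71² = 10.08 on 2 and 87 df. Power is 80.4% and the detectable d is 0.706, so the figure reproduces. No power is stated for the correlation aim.

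**Pooled r with no within-group link.** Inputs: 30 + 30 patients (from the article); within-group correlation 0; shifts of +d SD in the marker and -d SD in flow (assumed). For two equal groups

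r = -(d²/4) / (1 + d²/4)

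- d = 0.5: 0.0625/1.0625, so r = -0.06
- d = 0.71: 0.126/1.126, so r = -0.11
- d = 1.0: 0.25/1.25, so r = -0.20
- d = 1.5: 0.5625/1.5625, so r = -0.36

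For transit time, which would lengthen, the sign turns positive and the size is the same.

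Rejection rates come from simulation (two-sided 5% test, sidedness assumed; 40,000 runs, or 20,000 for Spearman):

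| d (SD) | Pooled Pearson | Pooled Spearman | Adjusted for group | Within one group |
|---|---|---|---|---|
| 0 | 5.1% | – | 5.1% | 5.0% |
| 0.5 | 7.4% | – | 5.1% | 5.0% |
| 0.71 | 13.8% | 13.7% | 4.8% | 5.0% |
| 1.0 | 34.6% | 34.4% | 5.1% | 5.1% |
| 1.5 | 85.2% | 87.0% | 5.1% | 4.9% |

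Adjustment or a within-group test removes the excess. Ranking alone does not.

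**What each reading can detect.** By Fisher's z, the correlation detectable with 80% power is tanh[(1.960 + 0.842)/√(n - 3)]: 0.35 at n = 60 and 0.49 at n = 30. A purely within-group analysis is free of the group effect but needs a much stronger correlation.

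**Skew.** Inputs (all assumed): n = 60, latent correlation 0.36 on the normal scale, 20,000 runs.

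| Data | Pearson power | Spearman power |
|---|---|---|
| Both normal | 82% | 77% |
| One log-normal, log SD 0.5 | 78% | 77% |
| One log-normal, log SD 1 | 65% | 78% |
| Both log-normal, log SD 1 | 52% | 77% |
| Both log-normal, log SD 1, latent correlation -0.36 | 32% | 77% |
| EDSS-like half-point scale, symmetric, against normal | 81% | 77% |
| EDSS-like, mildly skewed, against normal | 77% | 76% |
| EDSS-like, mildly skewed, against log-normal, log SD 1 | 61% | 76% |

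With no true correlation, Pearson kept about 5% rejection in all the log-normal cases. Skew costs power here; it does not create false positives. Ordinal scaling by itself costs nothing.

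**The case against.** **Pooling is not stated.** This is the strongest reply. A reader might infer that the plan commits to one r across all 60 patients. It does not: the outcome list ends with a plural reference to the patients' groups, which can mean each group on its own, and then the false correlation disappears. This stands. Pooling is only the more natural reading of the Abstract.

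**This is detail for an analysis plan.** A condensed article may leave covariates and transformations to a fuller document, and the article does promise to weigh treatment influence in the final analysis. That promise concerns therapy, however, not relapse status. The point here is the method that the article does state: one correlation coefficient, and a fallback that leaves correlations out.

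**The relapse–remission contrast may be part of the signal.** If the question is whether coagulation and flow move together as patients enter relapse, adjustment changes the question. This is fair. It argues for reporting the adjusted estimate and labelling any pooled one, not for leaving the two indistinguishable.

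**The sizes are assumed.** The 0.71 SD belongs to C4a in a three-group ANOVA; it is not an expected relapse–remission shift, still less one for perfusion. The article gives no SDs or distributions for these variables. Both stand, which is why ranges are shown.

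**Wider readings.** A reader might also infer that the ordinal EDSS makes Pearson weak, that lesion volume is affected, or that the number of marker-by-site tests is part of this defect. The simulation shows no loss from ordinal scaling alone, and no passage assigns EDSS to Pearson. Lesion number and volume are listed as a group comparison, outside the correlation aim. The count of tests is a separate question about an exploratory aim.

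**Conclusion.** The point holds in a limited form. The article names plain Pearson r as its only correlation method, states no handling of relapse status, and offers no rank or transformed alternative for correlations. If the 60 patients are pooled and relapse shifts both variables as hypothesised, a non-zero r is expected without any within-group link. Rejection is then about 7% at shifts of 0.5 SD, 14% at 0.71 SD and 35% at 1.0 SD, against a nominal 5%. These figures rest on pooling, on equal and opposite shifts, and on normal data.

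The loss of power is real only for markedly skewed markers, and how skewed these markers are is not documented. With near-normal data Pearson is slightly the better test.

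It would be wrong to conclude that the main comparisons are compromised. The correlation is an additional secondary aim. The primary marker comparisons and the C4a sample size do not depend on it, and the Conclusion itself expects group differences to be informative even if no correlation is found. The change is still worth making before analysis, because it replaces a stated method with a better one at almost no cost.

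**What to change.** For the coagulation–perfusion aim, amend Statistical Methods to:

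1. Report a correlation adjusted for relapse/remission status, either as a partial correlation or from a linear model of perfusion on the marker with a group term.
2. Show the relapse and remission estimates separately beside it.
3. Use log-transformed values or ranks where a marker is clearly skewed. This is in addition to the group adjustment, since ranks alone leave the group effect in place.
4. Label any pooled, unadjusted r as including the relapse–remission difference.

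The cost is a short paragraph and one degree of freedom. There is also a slight loss of power if ranks are used on near-normal data (77% against 82% in the case above). No new patients, samples or scans are needed.
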